## Abstract

**Background:**

High-calorie-expenditure training is common among endurance athletes and is an effective strategy for weight loss. Although many training protocols include walking, running, cycling, and swimming according to a target heart rate, there is limited research on high-calorie-expenditure interventions with multimodal training programs using quantitative methods.

**Objective:**

The aims of this research protocol are to (1) develop a high-calorie-expenditure training program to cover target calorie expenditure according to the trainability of women classified as overweight (according to a BMI of 25-29.9 kg/m^2^); (2) determine the effect of high-calorie-expenditure workouts on conditioning, glycemic variables, and body composition; and (3) evaluate the implementation of the intervention and results in comparison with outcomes obtained under a standard-calorie-expenditure training program.

**Methods:**

This is a randomized controlled trial with a pretest-posttest design. Participants include 33 women with a BMI in the overweight range (25-29.9) allocated to three groups: two intervention groups and one control group. The intervention will be conducted for 12 weeks. Participants in the first group will be assigned an exercise program with high energy expenditure of approximately 3000-3500 kilocalories/week in the form of 5 sessions per week with an intensity of 50%-75% maximum oxygen rate (VO_2_ max) and 60%-80% target heart rate. The second group will be assigned an exercise program with a standard energy expenditure of approximately 1200-1500 kilocalories/week with 3 sessions per week at an intensity of 60%-75% VO_2_ max, according to The American College of Sports Medicine guideline. The effects of the multimodal training program with daily tasks will be compared to those of the standard-calorie-expenditure and control (no exercise) conditions with respect to changes in glycemic indices and body composition. Daily calories will be calculated through the International Physical Activity Questionnaire and using Nutrition 4 software.

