## Methods

### Study Design

This study was designed to assess the effect of a 12-week multimodal exercise program intervention under two different calorie-expenditure conditions (high=3000 calories/week vs standard=1200 calories/week) and a no-exercise waitlist control group. The study was conducted at the University of Tabriz in the southeastern region of Azerbaijan, Iran. This study was registered in the Iranian Registry of Clinical Trials (IRCT20220202053916N1).

Figure 1 summarizes the proposed 12-week training plan. Participants will be allocated to three groups: a high-calorie-expenditure group, standard-calorie-expenditure group, and control group. In the high-calorie-expenditure group, participants will engage in 3 sessions of exercise per week for 45 minutes with an estimated expenditure of 650-900 calories per week for weeks 1 and 2. In the third week, they will also have 3 sessions per week with a training duration of 50 minutes per session at an estimated calorie expenditure of 750-1200 per week. In the fourth week, the duration of the exercise will be increased to 60 minutes with 3 sessions per week, thereby increasing the calorie expenditure of the exercise by approximately 1200-1300 per week. In the fifth and sixth weeks, the training time will increase to 70 minutes and the number of training sessions will also increase to 4 sessions per week, resulting in calorie expenditure of approximately 1800-1500 and 1600-2000 calories per week, respectively. In week 7, the training duration will increase to 4 sessions of 80 minutes each with estimated weekly calorie expenditure of 1800-2200. In weeks 8 and 9, the training duration will increase to 90 minutes with expenditure of 1900-2500 calories/week. In the last 3 weeks, the number of sessions will reach 5 with weekly sessions of 95, 100, 110, 110, and 110 minutes, respectively accounting for 2700-3100, 3000-3500, and 3300-3700 calories consumed in week 10, 11, and 12, respectively.

The standard-calorie-expenditure group will receive a 12-week exercise program in the form of 3 training sessions. In weeks 1 to 4, each session will comprise 40 minutes of exercise with 650-900 calories consumed per week; in weeks 5 to 8, sessions will last 60 minutes with 1000-1200 calories consumed per week; and weeks 9 to 12 will involve an increase in the training time to 80 minutes with expenditure of 1200-1500 calories per week.

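### End-of-programme weekly expenditure is presented as the 12-week dose of both arms, and the high arm's three stated progressions do not agree

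*Protocol article*

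**What the plan says.** The Methods paragraph of the abstract states "The intervention will be conducted for 12 weeks". It assigns the high arm "high energy expenditure of approximately 3000-3500 kilocalories/week in the form of 5 sessions per week" and the other exercise arm "standard energy expenditure of approximately 1200-1500 kilocalories/week with 3 sessions per week". It does not mention a ramp. Study Design opens by naming the two conditions "high=3000 calories/week vs standard=1200 calories/week".

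Three descriptions of how the high arm progresses follow.

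- **Study Design** gives a figure for every week. It starts with "3 sessions of exercise per week for 45 minutes with an estimated expenditure of 650-900 calories per week for weeks 1 and 2", goes to "estimated calorie expenditure of 750-1200 per week" in week 3, and ends with the sessions "respectively accounting for 2700-3100, 3000-3500, and 3300-3700 calories consumed in week 10, 11, and 12, respectively". Sessions rise from 3 to 4 in week 5 and to 5 in weeks 10-12. No count is given for weeks 8-9.
- **Table 3** starts at 750-1100 per week, first reaches 3000 in week 9 (3000-3200), and ends at 3800-4000.
- **The text of the High-Calorie-Expenditure Training Protocol section** calls 3000-3500 a goal and says it is reached once sessions have been lengthened over 2-4 weeks. It also says that sessions rise gradually from 3 to 5 per week.

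For the standard arm, Study Design gives 650-900 (weeks 1-4), 1000-1200 (weeks 5-8) and 1200-1500 (weeks 9-12).

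**The concern.** Weekly expenditure is the variable that defines the comparison. The pre-post outcomes are changes from before training to 2 days after the 12 weeks, so the exposure behind them is what was expended over the whole period. An abstract that sets 3000-3500 kcal and 5 sessions beside 12 weeks will be read, and coded in any evidence synthesis, as a 12-week dose. In Study Design the two arms have the same 650-900 kcal/week in weeks 1 and 2, and the high arm's range first lies wholly at or above 3000 in week 11.

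The end-phase figures also recur later. Results speaks of more than 3500 calories per week in the high arm. Comparison With Prior Studies gives 3700 and 1350 calories with no time unit, and session averages of 800 and 450 kcal. These sit at the end of the schedules: 4000/5 = 800 is the top of week 12 in Table 3 at 5 sessions, and 450 is the midpoint of week 12 in Table 2 (400-500). Limitations treats five weekly sessions as shown to be feasible, although Study Design states that frequency for three weeks only.

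**Working it through.** **Inputs.** Weekly ranges in kcal, reading calories as kilocalories. Week 5 in Study Design is printed in reverse order and is read as 1500-1800. Week 4 is worded as an increase by 1200-1300 and is read as a level.

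| Week | High, Study Design | High, Table 3 | Standard, Study Design |
|---|---|---|---|
| 1 | 650-900 | 750-1100 | 650-900 |
| 2 | 650-900 | 950-1200 | 650-900 |
| 3 | 750-1200 | 1170-1200 | 650-900 |
| 4 | 1200-1300 | 1200-1500 | 650-900 |
| 5 | 1500-1800 | 1800-2000 | 1000-1200 |
| 6 | 1600-2000 | 2000-2200 | 1000-1200 |
| 7 | 1800-2200 | 2300-2600 | 1000-1200 |
| 8 | 1900-2500 | 2400-2700 | 1000-1200 |
| 9 | 1900-2500 | 3000-3200 | 1200-1500 |
| 10 | 2700-3100 | 3200-3500 | 1200-1500 |
| 11 | 3000-3500 | 3700-3900 | 1200-1500 |
| 12 | 3300-3700 | 3800-4000 | 1200-1500 |

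**1. Where the label comes from.** The Study Design mean of weeks 10-12 is (2700+3000+3300)/3 = 3000 to (3100+3500+3700)/3 = 3433. The label reproduces as an end-phase level.

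**2. Twelve-week mean, high arm** (sum/12).
- Study Design: lower limits 20,950/12 = 1,746; upper limits 25,600/12 = 2,133; midpoints 23,275/12 = 1,940. Taking week 4 literally as an increment on week 3 adds 975 at midpoint: 24,250/12 = 2,021.
- Table 3: 26,270/12 = 2,189; 29,100/12 = 2,425; midpoints 27,685/12 = 2,307.
- Against the label midpoint of 3250: 1,940/3250 = 60% and 2,307/3250 = 71%.

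**3. The 2-4 week reading**, with Table 3 midpoints during the ramp and 3250 afterwards.
- Four-week ramp: (4,535 + 8 × 3250)/12 = 30,535/12 = 2,545.
- Two-week ramp: (2,000 + 10 × 3250)/12 = 34,500/12 = 2,875.
- Both schedules put week 4 at 1500 or less, so neither matches this reading.

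**4. Standard arm.** Study Design midpoints: 4 × (775 + 1100 + 1350) = 12,900; 12,900/12 = 1,075. Several lower limits in the weekly row of Table 2 appear to have lost a digit (for example 100-1300). Reading them as 1000-1200 gives 13,037.5/12 = 1,086. Using Table 2's session values times 3 instead gives 12,967.5/12 = 1,081.

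**5. Contrast over 12 weeks.**
- Labels: (3250 − 1350) × 12 = 22,800 (abstract); (3000 − 1200) × 12 = 21,600 (Study Design).
- Study Design schedules: 23,275 − 12,900 = 10,375, or 46%-48% of the labels.
- Tables 2 and 3: 27,685 − 13,037.5 = 14,647.5, about 14,650, or 64%-68%.
- Ratio of arms: 1.8 and 2.1, against 2.4 (3250/1350) and 2.5 (3000/1200).

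**6. Sessions, Study Design.** Weeks 1-4: 12. Weeks 5-7: 12. Weeks 10-12: 15. Weeks 8-9 have no stated count: 4 each gives 47/12 = 3.9, and 5 each gives 49/12 = 4.1. Table 3's 475 minutes in week 9 fits 5 sessions of 95 minutes, so the higher count cannot be excluded.

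**The case against.** The best defence is that nothing is concealed. Study Design prints the high arm's expenditure week by week, the training section calls 3000-3500 a goal and describes rising sessions, and the abstract condenses both arms to their final level in the same way. That stands. A reader might infer that the dose was never planned, or that the authors claim 3000-3500 in every week. The documents support neither: the level is planned as an end phase, and no sentence says every week.

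The size also depends on which progression holds. With the 2-4 week reading and the Study Design standard arm, the contrast is 30,535 − 12,900 = 17,635 to 34,500 − 12,900 = 21,600 kcal, far closer to the labels. With the upper limits throughout, the two-week version averages (1,100 + 1,200 + 10 × 3500)/12 = 3,108. This does not rescue the label, because both week-by-week schedules contradict that reading, but it shows why reconciliation comes first.

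Finally, a reader might infer that the randomised comparison is biased or that a planned effect-per-kcal estimate is distorted. Groups are compared as randomised whatever they are called, and no dose-response analysis is described. What is affected is the description of what was compared.

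**Conclusion.** The point holds as a labelling and consistency defect. The abstract and the Study Design label give end-phase levels as though they were the 12-week dose, and the article contains three incompatible progressions for the high arm. On either printed schedule the 12-week mean lies below 3000 at every bound (1,746-2,425 across the two), and the contrast is 46%-68% of what the labels imply. The two midpoint means, 1,940 and 2,307, belong to schedules that disagree and are not the ends of one range.

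The assumptions are midpoints as the typical week, the stated readings of weeks 4 and 5, the repaired digits in Table 2, and 4 or 5 sessions in weeks 8-9. None of them changes the direction. These are planned figures. They do not show what participants actually expended, so a reader should not infer from them that delivery fell short.

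**What to change.** 1. Reconcile the abstract, Study Design, the text of both training-protocol sections, and Tables 2 and 3. Which progression is right is for the investigators to say.
2. Describe both arms as progressive wherever the dose is named. Give the planned mean weekly and cumulative 12-week expenditure beside the peak level, with the number of weeks at the top level and at 5 sessions.
3. Report delivered cumulative kcal by arm from the per-session watch records described under Calorie Expenditure.
4. Interpret between-arm differences, and word Results, Discussion and Conclusions, against that cumulative figure rather than the peak week. Give a time unit to the 3700 and 1350.

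The cost is wording and summing data already collected. No outcome, sample size or analysis changes. On the present schedules the stated contrast becomes less favourable.

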**Results:**

Preliminary results show significant weight loss in both the high- and standard-calorie-expenditure groups (*P*=.003). Significant improvements were also found in muscle percentage (*P*=.05) and BMI (*P*=.05) for the high-calorie-expenditure group. Analyses are ongoing for glycemic indices, inflammation factors, and blood parameters.

**Conclusions:**

High-calorie-expenditure training can cause further weight loss than standard exercise, which can eventually lead to greater fat mass reduction and improvement in glycemic indices. These results demonstrate that, in some cases, it may be necessary to increase the activity of women and use multimodal exercise programs with increased volume and intensity to increase the expenditure of exercise and daily activity. We found a net effect of exercise and daily activity at the individual level, whereas the daily lifestyle and physical behaviors of the participants remained constant.

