The control group will not undergo exercise training, but will undergo the same blood tests, body composition measurements, appetite measurements, and nutrition and physical activity records as performed in the other two groups.

The schedule of data collection for the main outcome measures is presented in Table 1. Primary and secondary outcomes are measured 2 weeks prior to commencing the exercise training (baseline) and 2 days after completing the 12-week exercise or control period. We are also assessing the effectiveness of different types of exercise programs in mediating the risk of metabolic syndrome, including blood pressure disorders, increased blood lipids, uncontrolled blood sugar, obesity, and insulin resistance, with the goal of gaining a better understanding of the mechanism linking exercise to metabolic control. This is assessed by validating relevant formulas and other variables such as cardiovascular fitness and functional tests. Moreover, since high-calorie-expenditure exercise is associated with a goal of weight loss, there is a possibility that such a program will induce eating disorders, which is an issue that is more common in women. Therefore, two sessions were held for the participants to familiarize themselves with recording of daily food calories with the Eating Attitude Test-26 (EAT-26) questionnaire, including questions related to diet and appetite, in the 3 groups at 3 stages: before and during the course and at the end of the course. Body composition parameters were measured in the two training groups once every 2 weeks and in the control group before, in the middle, and at the end of the intervention. Blood parameters were also measured before and after the intervention to compare appetite levels. Performance tests were conducted before, during, and after the training period, and the calories consumed and physical activity were measured on a weekly basis.

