#### Physical Activity

The baseline physical activity of the participants will be assessed with the International Physical Activity Questionnaire (IPAQ) short form (7 items) and long form (IPAQ-L, 27 items) considering a reference period of the past 7 days. The IPAQ-L is a widely used tool that queries 5 activity domains independently and provides specific details on physical activity intensity levels, differentiating between usual weekdays and weekend days by measuring sitting time [20].

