#### Balance of Energy Expenditure and Energy Intake

Energy intake was recorded for each participant with daily energy intake obtained using the dietary analysis software Nutrition 4, version 1 [31].

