## Results

Preliminary results show that the high-calorie-expenditure training program more than doubled weight loss and reduced fat mass, along with a further decrease in waist circumference. Figure 3 shows the changes in the body composition of the three groups. The overall goal of increasing exercise energy consumption was achieved, with an increase in energy consumption in physical activity of more than 3500 calories per week in the high-calorie-expenditure group and up to 1200 calories per week in the standard-calorie-expenditure group. Preliminary statistical analyses indicate significant differences between the stages and in the interaction of time and group. Additional analyses of functional parameters, lipid profiles, inflammatory factors, and blood indicators are ongoing.

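### The abstract concludes that daily lifestyle and physical behaviors stayed constant, but no result by arm for energy intake or for activity outside the supervised sessions is shown

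*Protocol article*

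**What the plan says.** The Conclusions of the abstract report a net effect of exercise together with daily activity, "whereas the daily lifestyle and physical behaviors of the participants remained constant". This is worded as a finding, not as an assumption.

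The means to check it are planned. The Methods of the abstract state: "Daily calories will be calculated through the International Physical Activity Questionnaire and using Nutrition 4 software". Study Design says that "the calories consumed and physical activity were measured on a weekly basis", and Table 1 ticks physical activity and nutrition in every week from 1 to 12. The section on energy balance adds: "Energy intake was recorded for each participant with daily energy intake obtained using the dietary analysis software Nutrition 4, version 1". The Physical Activity section describes the IPAQ, for baseline activity, "considering a reference period of the past 7 days", and says of the long form: "The IPAQ-L is a widely used tool that queries 5 activity domains independently".

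The results shown are these. The abstract covers weight, muscle percentage and BMI. The Figure 3 caption lists BMI, weight, fat and muscle. The Results section and the Discussion give energy figures for the exercise programs. Of work still to come, Results says: "Additional analyses of functional parameters, lipid profiles, inflammatory factors, and blood indicators are ongoing". Limitations describes the IPAQ answers only as satisfactory, without figures.

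**The concern.** After randomization, women in an exercise program may eat more or less, or move more or less in the rest of the day. The article itself treats this as a live possibility: Study Design warns that the high-expenditure program could provoke disordered eating and schedules appetite and eating-attitude measures in all three arms. The Discussion calls earlier evidence on expenditure together with intake mixed.

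A claim that behavior did not change therefore needs data. Without them, a reader of the abstract will take the weight difference as the pure effect of exercise energy. What the shown results could support is narrower: the effect of being assigned to a program, including whatever changes in eating and daily movement came with it. The sentence also sits badly with itself, since it counts daily activity as part of the effect and then describes daily behavior as unchanged.

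**Working it through.** **Step 1. Look for a result behind the claim.** There is no stated figure for constancy to reproduce, so the places where one could stand are set side by side.

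| Place in the article | Intake by arm | Activity outside sessions by arm |
|---|---|---|
| Abstract, Results | none | none |
| Results section | none | none; more than 3500 v up to 1200 kcal/week, presented as the exercise goal achieved |
| Figure 3 caption | none | none |
| Discussion | none | none; 3700 v 1350 kcal, for the exercises performed |
| Limitations | none | none; IPAQ answers called satisfactory |

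Calorie Expenditure says that the watch measured each exercise session. It also describes a 24-hour energy calculation from activity factors, but no result of that calculation is reported.

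**Step 2. Could a total IPAQ score show constancy?** Assumption: the weekly activity measure is the IPAQ with its 7-day window. The window is stated for baseline; weekly use is inferred from the abstract's Methods, Study Design, Table 1 and Limitations. Session minutes falling inside one recall window:

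- Standard arm (Table 2): 120 in weeks 1-4, 155 in weeks 5-8, 190 in weeks 9-12.
- High arm (Table 3): 135 in week 1, rising to 530 in weeks 11 and 12.

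Study Design's session lengths imply even more in the standard arm late on (3 × 80 = 240 minutes). On either basis, a total score includes the sessions. It would rise with training even if the rest of the day did not change. Only a score with the sessions taken out could speak to constancy.

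**Step 3. Size of the planned exercise contrast.** The nominal contrast in Study Design is (3000 − 1200)/7 = 257 kcal/day, but both programs ramp up, so the 12-week average is the relevant figure. I take the midpoint of each weekly range, sum over 12 weeks, and divide the difference by 84 days.

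- Standard arm, Study Design: 4 × 775 + 4 × 1100 + 4 × 1350 = 12,900 kcal. (Table 2 is not used because several weekly totals from week 7 on are evidently misprinted, such as 100-1300.)
- High arm, Study Design: 775 + 775 + 975 + 1250 + 1650 + 1800 + 2000 + 2200 + 2200 + 2900 + 3250 + 3500 = 23,275 kcal.
- High arm, Table 3: 925 + 1075 + 1185 + 1350 + 1900 + 2100 + 2450 + 2550 + 3100 + 3350 + 3800 + 3900 = 27,685 kcal.

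Contrast from Study Design: (23,275 − 12,900)/84 = 124 kcal/day. Contrast with Table 3 for the high arm: (27,685 − 12,900)/84 = 176 kcal/day. The two sources for the high arm differ, so both are carried.

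**Step 4. What an unreported difference would mean.** The documents give no such difference, so these values are assumptions, shown as a range.

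| Assumed between-arm difference in intake or non-session activity | Share of 176 kcal/day | Share of 124 kcal/day |
|---|---|---|
| 50 kcal/day | 28% | 40% |
| 100 kcal/day | 57% | 81% |

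A difference of 124 to 176 kcal/day would equal the whole contrast. Set against the expenditure reported in the article, (3500 − 1200)/7 = 329 or (3700 − 1350)/7 = 336 kcal/day, 100 kcal/day is about 30%.

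**The case against.** The article labels its results preliminary, and the weekly records may well have been examined; the remark that the IPAQ answers were satisfactory points that way. That stands. A reader might infer that intake and activity were never analysed, but the documents support only that no result is shown. Likewise, that diet was left uncontrolled cannot be read from an article that describes recording and is silent on the rest.

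A reader might also infer that the abstract derives the exercise effect from constancy. The sentence sets the two statements in contrast and does not argue from one to the other, and it names exercise and daily activity, not exercise alone.

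The recall argument is conditional. The 7-day window is attached to baseline, nothing says that a total score was used, and the long form's separate domains may allow the sessions to be removed. How the questionnaire is scored is a detail that an article may leave to the full protocol.

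Keeping food and activity records could itself change behavior, but the control arm keeps the same records, so this does not by itself explain a difference between arms.

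Finally, in a randomized comparison, changes in eating or daily movement after allocation belong to the effect of assignment. They do not bias that comparison. This also stands, and it limits the point to the claim about behavior and mechanism. None of it supplies the missing result: randomization does not show that behavior stayed the same.

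**Conclusion.** The point holds as a claim without shown support. The abstract reports unchanged lifestyle and physical behavior as a finding, while the article contains no result by arm for intake or for activity outside the sessions.

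The planned 12-week contrast between the two exercise arms is modest, about 124 to 176 kcal/day, so a modest unreported difference would matter: 57% to 81% of the contrast at an assumed 100 kcal/day. This rests on range midpoints, the printed weekly ranges and an illustrative difference. No drift in either direction is documented, and the figures do not show that any occurred. The remark on the IPAQ total depends on its weekly use, which is inferred.

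This is a cheap improvement to what the trial concludes. It is not a flaw in the randomized comparison.

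**What to change.** From the data already scheduled weekly, report for each of the three arms, with 95% CI, the change over 12 weeks in recorded energy intake and in physical activity excluding the supervised sessions. State how the sessions were removed; if the IPAQ long form is the weekly measure, its separate domains are a natural starting point.

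Until those results are shown, delete the clause on constancy from the abstract's conclusion and describe the result as the effect of assignment to the program.

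The cost is a little extra analysis, no new data collection, and a weaker conclusion.
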